#### Retention

1. Monetary reimbursement for each data collection
2. Periodic phone calls to verify address and phone data
3. Use of secondary alternative contact information
4. Any “lost” individuals will be searched for using a comprehensive standardized web based search protocol which included:
  - a. Five people locators
  - b. Major social networking sites, specifically those with more minority involvement
  - c. Department of corrections database
  - d. These searches will be conducted on the target individual as well as secondary contacts
  - e. All potential contact will be private. No study related information will be conveyed in public through these searches.

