### **Transition and Retention**

Despite having "access" to healthcare, participants will be economically vulnerable individuals with uncontrolled diabetes. Ethically, we acknowledge that the "usual care" currently received often does not meet patients' needs or standards of care. Therefore, participants assigned to usual care will receive initial support to engage existing resources available through UI Health, such that healthcare providers will consider this an acceptable alternative upon randomization (clinical equipoise).

Upon randomization, participants will receive referrals to a diabetes educator and clinical pharmacist for medication reconciliation, adherence support, and education. Staff can schedule the visit at data collection. This is important as our prior work with medication reconciliation identified discrepancies in almost 60% of patients. A one-page list of clinic resources with names and direct telephone numbers (e.g., social worker) will be provided so they can more easily navigate the system. Finally, low-literacy, paper-based diabetes education information will be provided. At the end of year 1, these patients will cross-over and receive *mDAS*. Prior to this transition, HCs will work with the patients and their social support network to prepare them for the transition. Participants randomized to usual care will receive *mDAS* for one year.

*Retention strategies.* Participants will be reimbursed \$30 for each data collection. Participants assigned to the intervention in year one will receive an additional \$50 at 6 months and 12 months if they complete at least one videoconference before each data collection. Participants assigned to the intervention in year two will receive an additional \$50 at 18 months and 24 months if they complete at least one videoconference before each data collection. Participants who complete all five data collection visits and videoconferences with the pharmacist as described above will receive up to \$250 for completing the study.

*Additional Retention Strategies for mDAS Sleep Sub-study Supplement* Participants will be reimbursed an additional \$40 for participating in the sleep sub-study and turning in the wrist actigraph.

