*Temporary modifications to compensation during the COVID-19 pandemic.* Participants may choose to be paid through their preferred electronic pay app (such as QuickPay/Zelle, Venmo, or Paypal) OR a gift card of their choice from a list of online retailers such as Walmart, Target, Amazon, or Visa. Gift cards will be issued in the amounts as described above for each data collection visit and can be mailed, emailed or texted depending on the vendor.

Due to social distancing orders, participants will have the option to complete their HbA1c and cholesterol profiles using a home test kit. They may also choose to wait and come in to the CRC for a blood draw once research operations resume. Because of the added time and effort required for each of these options, an additional \$20 will be given to subjects for lab tests completed during the COVID-19 pandemic only. This additional incentive will not be offered once in-person interviews and phlebotomy resume.

Other retention strategies include: (1) periodic phone calls/ mailings to verify contact information; and (2) use of alternative contact information. We have developed a comprehensive standardized web-based search protocol that includes five people locators, major social networking sites including those with more minority involvement, and the department of corrections database. Searches are conducted on the target individual as well as alternative contacts.

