Cost and Healthcare Utilization Data: We will conduct a cost-utility analysis comparing *mDAS* with usual care, following the guidelines for conducting pharmacoeconomic analyses by the Panel on Cost-Effectiveness and Medicine and the International Society for Pharmacoeconomics and Outcomes Research. We will conduct the analysis from the health-system perspective, and include the costs of running the program as well as the costs associated with patient health services utilization. Costs will include pharmacists and HCs (training and implementation), educational materials, tablet computers with data service, text messaging, and videoconferencing. Health services utilization will include costs associated with hospital admissions, emergency room visits, outpatient visits and prescription medications during the intervention period. Participants will be followed throughout the study to obtain data on their programmatic and healthcare services related costs. At data collection points, research assistants will obtain the necessary information from patients on healthcare use outside of UI Health. We will capture UI Health care information electronically from the hospital electronic records and billing data for enrolled subjects. We have previously analyzed similar UI Health data. Additional costs (salaries for HCs, etc.) will be estimated from prevailing internal costs at the time. Cost estimations for healthcare use will be based on national Medicare reimbursement rates (average DRG rates) for hospitalization, Medicare fee schedules for physician and other professional services, and Medicare's Resource-Based Relative Value Scale for outpatient procedures. Since our study will span a period exceeding one year, appropriate costs will be discounted and adjusted for inflation.

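### In the randomised year only mDAS patients with a videoconference are paid $80 at the 6- and 12-month outcome visits and all others $30, an avoidable attendance incentive tied to arm and adherence

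*Protocol*

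**What the plan says.** The payment rules stand under Transition and Retention in section 6, in the paragraph on retention strategies:

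- Both arms: "Participants will be reimbursed \$30 for each data collection".
- mDAS arm, amount of the bonus: "Participants assigned to the intervention in year one will receive an additional \$50".
- mDAS arm, timing and condition of the bonus: "at 6 months and 12 months if they complete at least one videoconference before each data collection".
- Usual-care arm, after crossover: the same bonus "at 18 months and 24 months if they complete at least one videoconference before each data collection".
- Ceiling: a participant who completes all five data collections and the required videoconferences "will receive up to \$250 for completing the study".
- Pandemic supplement, both arms: "an additional \$20 will be given to subjects for lab tests completed during the COVID-19 pandemic only".

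The Retention list in section 6.1 mentions only "Monetary reimbursement for each data collection" and no condition on videoconference use. The pandemic paragraph on compensation treats the amounts as belonging to each data collection visit.

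Section 12.0 (Primary Outcomes) bases the first-year comparison on 0, 6 and 12 months. The same section plans intention-to-treat with imputation, plus a per-protocol analysis of complete cases that does not require the 6- and 18-month visits. The Pharmacy Management Protocol (part A, Appointment Scheduling) lets a patient who declines videoconferencing stay in the study with the health coach component alone.

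**The concern.** Attendance at months 6 and 12 decides whether A1c, blood pressure and LDL are observed for the randomised comparison. Over those months the bonus exists in one arm only and, within that arm, only for patients who used the pharmacist component. mDAS patients who decline videoconferencing can remain in the trial, so the Protocol foresees a group in the mDAS arm that is paid $30.

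The Protocol describes its participants as economically vulnerable, so an extra $50 on a base of $30 is a plausible reason to attend. If it works that way, the mDAS patients seen at month 12 would be enriched for engaged patients, and nothing comparable would act on the usual-care patients. If engaged patients also have better A1c for other reasons, a comparison of completers would lean towards mDAS.

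The two arms reach the same $250 ceiling over 24 months. That balance arrives only after the randomised comparison has ended.

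**Working it through.** **Step 1. Reproduce the stated ceiling.** Inputs: $30 per visit, five visits, $50 paid twice.

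5 × 30 + 2 × 50 = $250, as stated. The $50 is therefore added to the $30 and does not replace it.

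**Step 2. Payment in the randomised year.**

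| | Month 0 | Month 6 | Month 12 | Total |
|---|---|---|---|---|
| mDAS, videoconference before each visit | 30 | 30 + 50 = 80 | 80 | 190 |
| mDAS, no videoconference | 30 | 30 | 30 | 90 |
| Usual care | 30 | 30 | 30 | 90 |

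The ratio at each follow-up visit is 80/30 = 2.7. With the pandemic laboratory supplement the visit amounts become 80 + 20 = $100 and 30 + 20 = $50, so the $50 gap is unchanged.

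**Step 3. How large a bias could follow.** The Protocol gives a single drop-out allowance of 20%, not split by arm or engagement, so every input here is an assumption:

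- *e*, the engaged share of the mDAS arm: 60% or 75%.
- *r₁*, month-12 retention if engaged: 85% or 90%.
- *r₀*, month-12 retention if not engaged: 60% to 75%.
- *g*, the A1c advantage of engaged patients whatever the treatment: 0.3 to 0.8 points.
- No true treatment effect, and usual-care retention unrelated to engagement.

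Engaged share among mDAS completers: *s* = *e r₁* / [*e r₁* + (1 − *e*) *r₀*]. Bias in the completer difference: (*s* − *e*) × *g*.

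- Largest case (*e* = 0.60, *r₁* = 0.90, *r₀* = 0.60, *g* = 0.8): *s* = 0.54/(0.54 + 0.24) = 0.692; bias = 0.092 × 0.8 = 0.07.
- Smallest case (*e* = 0.75, *r₁* = 0.85, *r₀* = 0.75, *g* = 0.3): *s* = 0.6375/(0.6375 + 0.1875) = 0.773; bias = 0.023 × 0.3 = 0.007, about 0.01.

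Over the whole grid *s* runs from 63% to 82% and the bias from about 0.01 to 0.07 A1c points in favour of mDAS.

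**Step 4. Put it on the trial's scale.** The sample size paragraph in section 12.0 plans for a difference of 1.0 with SD 1.8. With 220 × 0.8 / 2 = 88 completers per arm, and ignoring clustering and repeated measures, SE ≈ 1.8 × √(2/88) = 0.27. A bias of 0.07 is 0.07/0.27 ≈ 0.26 of one SE.

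These figures describe the effect of an assumed gap in drop-out between engaged and unengaged patients. They do not isolate the part of that gap caused by the payment.

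**The case against.** The case for leaving the schedule alone has several parts.

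- **Attrition.** A reader might infer that the payment will make attrition differ by arm and keep only adherent mDAS patients. The Protocol does not show this. Other features also affect retention: usual-care patients have mDAS to look forward to after month 12, mDAS patients carry monthly home visits, and tracing applies to everyone. Even the direction of net differential drop-out is unknown. This stands.
- **Size.** Step 3 charges the whole retention gap to the payment, although engaged patients may well stay longer without it. It also assumes that motivated usual-care patients are not retained preferentially; if they are, part of the bias cancels. The condition is undemanding too. One videoconference before each visit is close to the Pharmacy Management Protocol's minimum of one pharmacist visit every six months, while the main text plans one every other month. With 90% engaged (assumed), and retention of 90% and 70%, engaged patients are 0.81/(0.81 + 0.07) = 92% of completers. With a 0.5 to 1.0 point advantage the bias is then 0.01 to 0.02. This stands as well.
- **Imputation.** It is tempting to say that imputation cannot repair engagement-driven drop-out. That goes too far. Section 8.0 and Table 4 record videoconferences, so engagement can inform imputation within the mDAS arm. It has no counterpart in first-year usual care, however, so it cannot serve as a common adjustment covariate. The complete-case analysis gets no help from imputation.
- **Costs.** It is also tempting to say that the cost analysis wrongly leaves the incentive out. Section 8.0 says "Costs will include pharmacists and HCs (training and implementation), educational materials, tablet computers with data service, text messaging, and videoconferencing" and then adds further costs in open-ended terms. The list is not shown to be exhaustive, and a retention payment may reasonably be treated as a research cost.

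None of this supplies a reason for paying the bonus at the outcome visit.

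**Conclusion.** The payment asymmetry is certain: $80 against $30 at both follow-up visits of the randomised year, and $190 against $90 by month 12, with nothing to offset it before crossover. It creates a risk of differential, engagement-related attrition that can be avoided at little cost.

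The size of any resulting bias cannot be determined from the Protocol. Under the assumptions shown it is roughly 0.01 to 0.07 A1c points against a planned 1.0, and the payment's own share would be smaller if engaged patients stay longer anyway. The complete-case per-protocol analysis is the most exposed, because attendance at month 12 decides who enters it for the first-year comparison. Intention-to-treat with imputation is less exposed if the imputation uses videoconference history in the mDAS arm.

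The documents do not support the conclusion that the trial's A1c result will be materially biased. This is a design improvement worth making.

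**What to change.** Amend the retention paragraph under Transition and Retention:

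1. Pay the same amount for each data collection to every participant, whatever the arm and whether or not a videoconference has taken place.
2. If the $50 videoconference incentive is kept, pay it when the videoconference is completed and not at the outcome visit: in year 1 for the mDAS arm and in year 2 for the crossover group. Say which videoconferences qualify, since the present wording can be read as letting one early videoconference count for both payments.

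With $30 per visit and two payments of $50, the maximum stays at $250. The incentive to use videoconferencing is kept, and the gap at each outcome visit falls from $50 to $0.

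As a minor clarification, state in the cost paragraph of section 8.0 whether the incentive, up to $100 per participant, counts as a programme cost or a research cost.

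The cost is a payment-schedule amendment and slightly higher expected spend, because some patients will earn the $50 without attending the next visit. There may also be a little less pull to attend in the mDAS arm.

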## **7.0 Expected Risks/Benefits**

### Risks and Protections

The main risks include: (1) a small risk that subjects will have blood sugar or blood pressure levels that are too low or too high; (2) a small risk that the confidentiality of the subjects' records will be breached; (3) a small risk that subjects will feel annoyed by receiving study text messages; and (4) a small risk that a subject will experience pain or bruising at the site where blood is drawn for phlebotomy (less common risks include fainting, the formation of a small blood clot or swelling of the vein and surrounding tissue, bleeding from the site, and infection). It is unlikely that any of these risks would result in serious consequences. For all patients, an alternative to enrolling in the study is not participating (patients may continue usual health care services at UI Health outside of the study, including diabetes education).

Additional risks for those enrolled in the sub-study include a small risk the patients may develop a rash, irritation, or discomfort from wearing a wrist actigraph for 7 days/nights.

HIPAA regulations focus more on minimizing and managing risk rather than the actual information technology utilized. We will utilize a comprehensive approach to maximize data security for videoconferencing and text messaging services. Protected health information (PHI) will be exchanged through videoconferencing but not in text messaging. We will include an information privacy and security committee to advise, assist, and monitor our research policies using technology and for documentation. The committee will include an IT security expert, privacy official, and a clinician from UI Health. The committee will: (1) conduct a formal risk analysis; (2) develop a risk management strategy based on risk analysis; (3) implement strategy and train staff; and (4) monitor risk continuously. Text messages will have the health coach name pre-pended to messages to remind participants they come from health coaches (e.g., "[name]: Just a friendly reminder – it's time for your meds, Carol."). Patients will be reminded that text messages are sent in an automated fashion by computer. Thus, any replies may not be read immediately. Text messaging by patients should not be considered an Emergency Response System. Furthermore, they will be reminded that urgent health questions should be directed to their physician and not sent in a text message. HCs will monitor daily message feeds containing routine responses from patients.

*Extreme Blood Sugar or Blood Pressure Levels:* If a patient takes too much or too little medication, blood sugar and blood pressure levels may be too low or too high. The expected frequency of experienced side effects among participants is comparable as those receiving usual care taking the same medication. However, greater intensification of therapy could potentially increase this risk. To minimize risk, pharmacists and PCPs follow standard algorithms for glycemic and blood pressure management (i.e., American Diabetes Association and Joint National Committee on Prevention, Detection, Evaluation, and Treatment of High Blood Pressure) and use standard precautions in adjusting therapy: (1) addressing side effects (e.g., hypoglycemia) during every patient contact; (2) applying principles of aggressive therapy (education, empowerment, self-monitoring, flexible medication regimen, individualized goals, professional guidance); and (3) considering risk factors for hypoglycemia or hypotension. HCs also receive specific training on how to respond to extreme blood sugars and blood pressures if this occurs during a visit. They will be trained to respond in manner that is appropriate for their positions as trained lay-people.

Currently, at least one-third to two-thirds of patients with diabetes do not take their diabetes and hypertension medications correctly. In contrast, study participants will receive greater monitoring and support than other patients receiving usual care, which may help them

take medication more properly. The study procedures will allow for medication adjustment in a logical, conservative fashion, whereas many patients may adjust therapies on their own, or with infrequent or ineffective provider contact, not adjust at all. All pharmacists and health coaches receive extensive training and monitoring to deliver appropriate assistance to patients. We have implemented additional protection with PCP (or covering physician) contact if necessary at any time, day or night. Based on the frequent contact and monitoring involved, participants have less extreme blood sugar or blood pressure levels than those receiving usual care.

*Poor Information:* It is possible that subjects may receive and act on inaccurate information or misinterpret accurate information given the team approach and novel communication methods utilized. However, it remains more likely that there is a greater risk of misinformation from providers when additional support is not available, especially due to language and cultural barriers. To address this, HCs receive training and ongoing evaluation to reduce the risk of providing misinformation. HCs serving Latino patients will be bilingual, and all communication as well as informational materials will be in either English or Spanish to avoid a potential language barrier. In addition, HCs work closely with pharmacists and communicate regularly, providing a means to obtain accurate information and receive prompt and clear answers to their questions. To address any possibility for subject concern regarding information received, we will encourage them to seek help from their primary care physician (PCP) and pharmacist if they are uncomfortable with any of the information provided by health coaches.

*Breach of Confidentiality:* There is a small risk of breach of confidentiality, regarding health information and collected research data. All research staff, including pharmacists and HCs, will have formal IRB human subject protection and HIPAA training. Additional HC training includes discussions on maintaining confidentiality of health information, including communication with health providers. For data collection, all subjects will be assigned a blind code number. These lists will be kept in a locked file and will not be shown to staff. Data collected from computer use files will have the name removed and the code number attached by the research coordinator. Project staff who have access to the data will not have access to subject names. No clinical staff who have direct contact with the subjects will have access to research data. Finally, there will be no personal information stored on the server itself; and all e-mail communication will be encrypted and secure.

*Videoconferences* will be conducted through VSee. VSee provides real-time person-to-person audio and video communications. It is most suitable for health-related communication, as it is FDA registered and HIPAA compliant. VSee uses 256-bit AES (Advanced Encryption Standard) and “peer-to-peer” sessions so information is not stored on a VSee server. Although VSee allows for local file storage which may be considered electronic personal health information (e-PHI), UI Health does not currently have electronic storage of such communications into the electronic medical record. Pharmacist notes abstracting the relevant details of the videoconference encounter will be recorded in the medical records. Overall, the risk of accidental disclosure of e-PHI is very small.

*Text messages* will not include any identifying information nor will any personal health information be disclosed by our team. Patients will be instructed not to use text messaging to share health information. Patients will be reminded that text messages are sent in an automated fashion by computer. Thus, any replies may not be read in a timely fashion. Text

messaging by patients should not be considered an Emergency Response System. Furthermore, they will be told and reminded that urgent health questions should be directed to their physician and not sent in a text message. If an individual does share e-PHI through text messaging, the information will be permanently deleted and the patient will be educated regarding this process.

*Feeling annoyed by text messages:* Subjects will receive regular scheduled text messages during the study. Participants who no longer wish to receive reminders or text messages may reply with “STOP.” Twilio automatically will block *mytapp* from sending messages if this is received; thus, messages will be immediately discontinued without requiring contact with research team. However, patients have the option to re-subscribe with “START” again and resume messages. *mytapp* also color-codes blocked messages as “red” which will be easily detected by health coaches. This allows the HCs to identify problems including loss of mobile service.

*Phlebotomy:* Subjects may have pain or bruising at the site where blood is drawn for phlebotomy. Less common risks include fainting, the formation of a small blood clot or swelling of the vein and surrounding tissue, bleeding from the site, and infection. The Clinical Interface Core (CIC) employs health professionals for all phlebotomy services. *Home test kits:* Subjects may experience very brief discomfort after the finger stick and from squeezing drops of blood into the sample well. This will be comparable to the pain they experience when they undergo glucose testing. Alcohol pads, gauze and bandaids are provided with each kit to keep the site clean. Tips for minimizing discomfort and increase blood flow are included in the kit and instructional video online.

While unlikely, there is a slight risk that a participant may indicate thoughts of suicide or self-harm by scoring a 2 or 3 on item 9 of the PHQ-9 questionnaire. If this occurs, the data collector will contact [name] on her cell phone immediately upon completion of the interview or during a break in the interview (if appropriate). [name] is a trained clinical psychologist and as such will come to the CIC, meet with the patient and evaluate if further action is needed to ensure the participant’s safety. If [name] is unable to be reached, [name] will be paged or reached by cell phone. [name] or [name] will assess the participant including suicidal ideation, intent, and plan. Then, [name] or [name] will intervene appropriately, which may include providing resources for mental health support, facilitating referral to psychiatry, or immediately escorting the participant to the UI Health emergency room if urgent evaluation/intervention is needed to ensure personal safety, security, and stability.

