Goals set jointly by HC and patients are SMART (specific, measurable, achievable, relevant, and time-specific). Action plans are culturally tailored to subject individual needs, preferences, and resources. African-American HCs will highlight specific activities and resources in African-American communities. Likewise, Latino HCs include Spanish text messages (if Spanish is the preferred language) and different community-based resources and educational materials. Activity choices may include routine medication use, food choices, physical activity, stress reduction, smoking cessation, or other behavioral targets. Subjects indicate their level of confidence in success to help refine the frequency and intensity of activity through motivational interviewing techniques. HCs will help their patients anticipate barriers, discover potential solutions, and establish follow up plans. They employ problem-solving strategies and engage community resources as needed.

Text messaging will further enhance HCs' ability to support their patients. They will direct messages to maintain motivation, elicit feedback on progress, and screen for barriers that may reduce chance of success. For example, a morning text message may ask a patient how they did on their goal the previous day. Responses may be "yes/no", a rating scale, or other measure of activity. The subject will receive an automated response based on progress made, and additional messages (tips/problem solving messages) if not achieving goals. No more than seven messages will be delivered weekly, except for optional medication reminders.

| Example Text Message Templates |               |                                                                       |
|--------------------------------|---------------|-----------------------------------------------------------------------|
| Message Type                   | Frequency     | Example                                                               |
| Medication Reminder            | 1-4 times/day | "Hi, [name], just checking to see if you took your morning pills." |

|                      |          |                                                                        |
|----------------------|----------|------------------------------------------------------------------------|
| Refill Reminder      | Monthly  | "Make sure you don't run out. Check to see when a pill refill is due." |

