| Appointment Reminder | Variable | "Just a reminder that you have a doc's appointment today."             |
| Goal Monitoring      | Variable | "Remember your goal. Did you take your meds last night?"               |
| Glucose Monitoring   | Variable | "Hello, [name], have you had time to check your sugar today?"     |
| Self-Efficacy        | Weekly   | "Taking your meds is within your control. You can do it."              |
| Motivation           | Weekly   | "You have come a long way! Keep up the good work!"                     |

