*VSee videoconferencing* uses “peer-to-peer” sessions so information is not stored on a VSee server. VSee uses 256-bit AES (Advanced Encryption Standard) for secure transmission of information. Text messaging will not be secure and will not contain e-PHI. However, *mytapp* includes multiple security measures. Limited subject information will be available on *mytapp*, such as name and study ID number, and telephone number stored in an encrypted PostgreSQL database. We utilize TLS (Transport Layer Security) with encryption for all *mytapp* interactions and interactions with Twilio. All information from Twilio to *mytapp* is validated against embedded digital signatures to ensure authenticity and prevent “spoofing.” A “PaperTrail” application provides a continuous audit trail to monitor *mytapp* use and all message activity. We will utilize a comprehensive approach to maximize privacy and data security for videoconferencing and text messaging services. We will include an information privacy and security committee to advise, assist, and monitor our research policies using technology and for documentation. The committee will include an IT security expert, privacy official, and a clinician from UI Health. The committee will: (1) conduct a formal risk analysis; (2) develop a risk management strategy based on risk analysis; (3) implement strategy and assist in training staff; and (4) monitor risk continuously.

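### The protocol promises that texts carry no identifying or personal health information, but its own sample messages address patients by name in medication and glucose prompts

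*Protocol*

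**What the plan says.** Section 7.0 (Risks and Protections) lists a confidentiality breach among the four main risks. For texting it gives a content rule as protection: messages "will not include any identifying information nor will any personal health information be disclosed by our team". An earlier paragraph of the same section says: "Protected health information (PHI) will be exchanged through videoconferencing but not in text messaging". Section 11.0 repeats the point and describes the channel: "Text messaging will not be secure and will not contain e-PHI".

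The intervention is described in section 6.4 (Text Messaging). Coaches schedule messages about visits, medicines and goals. A table of example templates follows, with seven message types. The medication reminder greets an addressee and continues: "just checking to see if you took your morning pills". The glucose template also opens with a greeting by name and asks: "have you had time to check your sugar today". Section B.2 of the appended pharmacy management protocol has the coach text the patient, in the two weeks before a pharmacist videoconference, to check and log blood sugars.

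The data-security paragraph of section 7.0, which carries the rule on protected health information, also prints a sample text. It begins with the coach's name and ends a medication reminder with the patient's first name.

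**The concern.** The safeguard is worded absolutely and covers a channel that the protocol itself calls insecure. An ethics reviewer or participant who reads only the risk section would conclude that an intercepted or overseen text reveals neither who the patient is nor anything about their health. Someone who reads section 6.4 would expect texts that use the patient's name and refer to pills, blood sugar and medical visits. If messages go out in the form the protocol illustrates, participants do not have the protection it states. If the safeguard is applied as written, at least the name-bearing messages have to change.

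**Working it through.** The protocol gives no figure to reproduce on this point. The check sets the rules beside the messages.

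| Place | Rule or message | Patient name | Health-related content |
|---|---|---|---|
| 7.0, text messages paragraph | rule | barred, no exception | personal health information barred, not defined |
| 7.0, data-security paragraph | rule | not addressed separately | PHI barred from texts, not defined |
| 11.0 | rule | not addressed separately | e-PHI barred; channel not secure |
| 7.0, sample message | text | yes, first name | generic medication prompt |
| 6.4, medication reminder | text | yes, in greeting | pills |
| 6.4, refill reminder | text | no | pill refill |
| 6.4, appointment reminder | text | no | doctor's visit that day |
| 6.4, goal monitoring | text | no | medication taken or not |
| 6.4, glucose monitoring | text | yes, in greeting | blood sugar check |
| 6.4, self-efficacy | text | no | taking medication |
| 6.4, motivation | text | no | none |

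**Names.** Two of the seven templates and the section 7.0 sample use a patient name. In the two templates the name has been removed from the public copy, but its place directly after the salutation shows that it is the addressee's. The section 7.0 sample, where the patient's first name is still visible, confirms the practice. The coach's name at the start of a message is not counted, since it does not identify the patient. A rule that excludes identifying information of any kind does not allow for a first name, so this part of the conflict needs no further interpretation.

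**Health content.** By subject, 7 − 1 = 6 templates concern medication, refills, glucose or a medical visit. Whether they breach the rule depends on the meaning of the barred term:

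- *Narrow reading* (a specific drug, dose, value, result or diagnosis): 0 of 7 templates breach the health-content rule. The two name-bearing templates and the sample still breach the rule on identifying information.
- *Broad reading* (any indication that the recipient takes medication, checks glucose or has a medical visit): 6 of 7 templates and the sample breach it.

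**Is it only sample wording?** For names, yes: the table is headed as examples and the greeting can be dropped. For health subject matter, no: section 6.4 makes medicines and visits part of what coaches schedule, and the pharmacy protocol requires glucose reminders by text. On the broad reading the conflict is therefore with the planned intervention as well as with the illustrations.

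**The case against.** The best defence is that the authors never meant generic prompts to count as protected information. The paragraph that says PHI "will be exchanged through videoconferencing but not in text messaging" prints a medication reminder of its own, which points to a narrow meaning. The messages go to the patient's own phone and state no drug, dose, reading or diagnosis. This has force, and it is why the health-content part cannot be put as a certain breach. It does not rescue the name, which the text messages paragraph excludes without qualification.

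The content rule is also not the only protection. The protocol describes confidentiality training, a privacy and security committee charged with a formal risk analysis, encrypted storage with an audit trail on the texting platform, and an opt-out by reply. These reduce the risk, but they do not make the statement about message content accurate.

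A reader might go further and infer that the safeguard and the text intervention are incompatible in principle. The documents do not support that: the templates are examples, coaches tailor every message, and on the narrow reading dropping the name is enough.

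A reader might also infer that content would differ from coach to coach according to which section each one follows. Nothing in the protocol shows this. Section 6.4 provides standardized training in texting and its safety procedures and has the coordinator monitor all texting activity, and section 8.0 has message data reviewed monthly for fidelity.

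**Conclusion.** The protocol contradicts itself on what its texts contain. On names the contradiction is plain: two of seven templates and the section 7.0 sample. On health content it ranges from none to six of seven templates, depending on a definition that the protocol does not give.

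The consequence is limited to participant confidentiality and the accuracy of the risk as stated. Randomization, the A1c comparison and the sample size are untouched.

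It is tempting to size the exposure by message volume. One to four medication reminders a day for 365 days in 110 patients (half of 220) would give 1 × 365 × 110 = 40,150 to 4 × 365 × 110 = 160,600 messages. The documents do not support this as a measure of harm. Section 6.4 makes medication reminders optional, no uptake is given, and a message count says nothing about how many would disclose anything. Nor can it be said that participants are misinformed in the consent form, because that form is not available.

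The conclusion rests on reading the greeting position in the two templates as the patient's name, which the section 7.0 sample supports.

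**What to change.** Bring section 6.4 (text messaging and its templates), both texting paragraphs of section 7.0, and section 11.0 under one rule that defines what a study text may contain. There are two ways to do so:

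- Remove patient names from the two templates and the section 7.0 sample, and state that generic medication, glucose and appointment prompts are sent over an unsecured channel.
- Keep the messages, and correct the safeguard in sections 7.0 and 11.0 to say which name and health content is texted.

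In either case, check that the consent wording matches. The existing coach training and message review can carry the rule, so no new procedure is needed.

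The cost is a minor protocol and template amendment. The first route makes messages somewhat less personal; the second makes the stated protection less favourable.
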